### Statistical Methods

We will undertake descriptive analysis of the swabbing rates and swab positivity rates from the study practices. This includes analysis of the demographic and clinical characteristics of those presenting with RTI symptoms and those with confirmed influenza infections in primary care. We will also report the number of patients who have also undertaken swabbing for reference laboratory analysis in addition to POCT testing in study practices. In those study practices that also take part in virological surveillance, these reference laboratory swabs are reported to the UKHSA as part of national disease surveillance.

To answer our primary objective, we will calculate the crude odds of antimicrobial prescribing (all antibiotics and all antivirals regardless of type), given a POCT diagnosis of influenza is the probability of antimicrobial prescribing given a particular POCT test result. We will record whether the antimicrobials were given within 7 days of the POCT diagnosis or within 30 days of diagnosis. We will calculate the crude odds ratio by dividing the odds of antimicrobial prescribing in people who receive a positive influenza POCT result by the odds in people who receive a negative test result.

We will also calculate the adjusted odds ratio using a logistic regression model. We will use the following set of covariates that are known to be associated with the severity of influenza and are collected from the routine data extracted from the electronic health record: age, sex, ethnicity (reported in 5 categories: White, Asian, Black, other, or mixed; maximized using an ontology [30]), socioeconomic status (measured using the index of multiple deprivation [31], which is a nationally available measure assigned based on post code), any of these chronic underlying conditions (chronic pulmonary disease, cardiovascular disease, diabetes, liver disease, renal disease, neurologic or neuromuscular conditions, treatment-induced immunosuppression, and disease-induced immunosuppression), number of GP visits in the 12 months prior to the study period describing a study participant’s health care–seeking behavior, number of hospitalizations in the 12 months prior to the study period (used as proxy for the severity of the chronic conditions), influenza vaccination in previous influenza seasons (at least one), pregnancy, use of influenza antivirals, and pneumococcal and COVID-19 vaccination status.

To answer our secondary objective, we will select a matched set of practices from the rest of the English national sentinel network based on practice size, average age of registered patients, proportion of registered female patients, and number of GPs employed during the study.

The rates of hospital referrals and deaths related to influenza infection within 30 days of diagnosis will be compared between PIAMS study practices and the rest of the network using the ANOVA test.

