**Results:**

We will present the crude and adjusted odds of antimicrobial prescribing (all antibiotics and antivirals) given a POCT diagnosis of influenza, stratifying by whether individuals have a respiratory or other relevant diagnosis (eg, bronchiectasis). We will also present the rates of hospital referrals and deaths related to influenza infection in PIAMS study practices compared with a set of matched practices in the sentinel network and the rest of the network. We will describe any difference in implementation models in terms of staff involved and workflow.

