## Introduction

### Rapid Testing for Influenza in a Postpandemic Health Service

Measures to limit SARS-CoV-2 transmission during the COVID-19 pandemic coincided with a marked decrease in infections caused by other respiratory viruses [1,2].

After the lifting of COVID-19 containment measures, the robust return of influenza, seasonal coronaviruses, parainfluenza virus, and respiratory syncytial virus (RSV) was observed in many countries including the United Kingdom [3].

Figure 1 and Table 1 show data from the English national sentinel surveillance network as of the end of November 2022. Influenza and RSV were the main circulating respiratory viruses, with SARS-CoV-2 making up only 12.4% (15/121) of the total number of laboratory-confirmed cases.

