**Figure 1 figure1:**
[figure not shown]
Swab positivity by week in the English national sentinel surveillance network from March 2022 to January 2023 [4]. hMPV: human metapneumovirus; RSV: respiratory syncytial virus.

In the context of a postpandemic health care service where there are high levels of circulating influenza, accurate, rapid molecular diagnostic test platforms have the potential to (1) improve clinical decision-making regarding the use of antibiotics and antivirals, (2) improve patient outcomes due to the early appropriate use of antivirals, and (3) provide better information to inform sentinel surveillance and clinical research including studies of vaccine effectiveness and real-world trials [5,6].

Specifically, for patients with influenza infection, early diagnosis and administration of antivirals may improve clinical outcomes [7,8]. They may also limit symptom duration and spread to household contacts, and newer antivirals for influenza, such as baloxavir, have been shown to improve the time to resolution of symptoms and reduce complications in high-risk patients [9].

Currently, only a small proportion of patients with respiratory tract infections (RTIs) undergoes diagnostic microbiological testing before receiving treatments in primary care [10], and there is evidence of widespread variations in antimicrobial prescribing practices [11]. This is important, as prescribing in primary care accounts for about 8% of National Health Service (NHS) expenditure, which is equivalent to over £9 billion (US $11.1 billion) per year, with just over £220 million (US $271.5 million) being spent on antimicrobials [12]. Inappropriate prescribing of antimicrobials and unwarranted variation in prescribing can contribute to increase of antimicrobial-resistant strains and patient adverse events in the short and long term [13].

We have previously shown that, in a prepandemic context, it is feasible to undertake point-of-care testing (POCT) for influenza in primary care in the England, with promising impacts on antimicrobial use and estimates of influenza vaccine effectiveness that are comparable with published data [14-16]. However, its impact on more severe outcomes such as hospitalization and mortality following infection has not been reported.

Recent work on in-pandemic prescribing of azithromycin and doxycycline for RTIs across the sentinel network has shown scope for measures to improve antibiotic stewardship in primary care [17].

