### Objectives

This study aims to report the impact of POCT for influenza on antimicrobial prescribing in primary care. We will additionally describe severe outcomes postinfection (hospitalization and mortality) and how POCT is integrated into primary care workflows.

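### The antiviral outcome counts every antiviral, not only those for influenza, which pulls the positive-versus-negative odds ratio towards 1 by an unknown amount; the antibiotic counterpart is minor

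*Protocol article*

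**What the plan says.** The Objectives section sets the question: "This study aims to report the impact of POCT for influenza on antimicrobial prescribing in primary care". The Introduction gives the antiviral part of the rationale: "Specifically, for patients with influenza infection, early diagnosis and administration of antivirals may improve clinical outcomes".

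For the primary objective, Statistical Methods then fixes the outcome as follows: "we will calculate the crude odds of antimicrobial prescribing (all antibiotics and all antivirals regardless of type), given a POCT diagnosis of influenza". On timing it says "We will record whether the antimicrobials were given within 7 days of the POCT diagnosis or within 30 days of diagnosis". The contrast is described as "dividing the odds of antimicrobial prescribing in people who receive a positive influenza POCT result by the odds in people who receive a negative test". The same section lists use of influenza antivirals among the adjustment covariates taken from the health record.

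Three other places bear on the point:
- Sample Size Calculation defines the primary outcome more narrowly, as the share of RTI consultations at which any antibiotic is prescribed. Antivirals are not part of it.
- The Results paragraph of the Abstract promises to present the odds "stratifying by whether individuals have a respiratory or other relevant diagnosis (eg, bronchiectasis").
- The Introduction describes other viruses in circulation in the last tabulated week, "with SARS-CoV-2 making up only 12.4% (15/121) of the total number of laboratory-confirmed cases".

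**The concern.** The test tells the clinician whether the patient has influenza. The antiviral response it can be expected to produce is an influenza antiviral in a patient who tests positive. An antiviral for a different virus says little about that response, yet the stated outcome counts it.

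Two mechanisms follow, and they should be kept apart:
- **Antivirals unrelated to the respiratory illness** can occur in either group. They add a similar small proportion of events to both and dilute the odds ratio.
- **Antivirals for another respiratory virus** go mainly to patients whose illness is not influenza, who make up the comparator. This error depends on the exposure. Adjusting for baseline covariates does not remove it, because the misclassification is in the outcome.

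Both pull an antiviral odds ratio above 1 towards 1. At stake is the readability of the antiviral result: a modest odds ratio could mean that the test changed little, or that other antivirals were counted in the negatives.

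For antibiotics, long-term prophylactic items and courses for unrelated infections also count. There is no clear reason for these to differ by influenza result, so they only dilute.

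**Working it through.** The plan states no figure on this point, so there is none to reproduce. Every prescribing rate below is an assumption; only the virus counts come from the documents.

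**1. Is the outcome restricted anywhere?** Statistical Methods includes all antibiotics and all antivirals. Sample Size Calculation ties antibiotics to RTI consultations, but the analysis text does not carry that tie over. The Abstract's stratification groups patients by their diagnosis and removes no prescription from the outcome. No section limits antivirals to influenza agents. The covariate list shows that influenza antivirals can be identified in the data.

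**2. Could the comparator contain other treatable viral illness?** From Table 1 (818 positive swabs, 215 influenza, 196 SARS-CoV-2):
- whole period: 196 / (818 − 215) = 196 / 603 = 32.5% of non-influenza positives
- last week: 15 / (121 − 26) = 15 / 95 = 15.8%

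These are shares of virus-positive swabs. Influenza-negative patients also include people with no virus detected, so the share among them is lower. The SARS-CoV-2 share of all positives was also falling, from 57.7% to 12.4% over the tabulated weeks.

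**3. Antivirals, comparator only.** Let a be the proportion given an influenza antiviral and q the proportion of negatives given another antiviral. Then P(any | negative) = 1 − (1 − a)(1 − q), and the odds ratio is odds(positive) / odds(negative).

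| Influenza antiviral, positive v negative | q = 0 | q = 1% | q = 2% | q = 5% |
|---|---|---|---|---|
| 20% v 1% | 24.8 | 12.3 | 8.1 | 4.0 |
| 10% v 2% | 5.4 | 3.6 | 2.7 | 1.5 |

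**4. Antivirals, separating the two mechanisms.** Assume influenza antivirals in 10% of positives and 0.5% of negatives.
- Start: (0.10/0.90) / (0.005/0.995) = 22.1.
- Add other antivirals in 0.5% of both groups: positives 1 − 0.90 × 0.995 = 10.45%, negatives 1 − 0.995² = 0.9975%; odds ratio 11.6.
- Add antivirals for another respiratory virus in 0.5% of negatives: negatives 1 − 0.995³ = 1.49%; odds ratio 7.7.
- With 2% in place of that 0.5%: negatives 1 − 0.995² × 0.98 = 2.98%; odds ratio 3.8.

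On the log scale the non-differential step alone is ln(22.1/11.6) = 0.64. The total fall is ln(22.1/7.7) = 1.05 to ln(22.1/3.8) = 1.76. So 61% down to 37% of the fall is ordinary dilution, not differential error. On the absolute scale the difference moves from 9.5 points to 10.45 − 1.49 = 9.0, or to 10.45 − 2.98 = 7.5.

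**5. Antibiotics.** Use the 5-point difference from Sample Size Calculation with assumed levels of 18% in positives and 23% in negatives, and unrelated courses in a proportion b of both groups: p′ = 1 − (1 − p)(1 − b).
- b = 0: 0.73
- b = 3%: 20.5% v 25.3%, odds ratio 0.76
- b = 10%: 26.2% v 30.7%, odds ratio 0.80

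**The case against.** Counting all agents is a defensible stewardship measure. Statistical Methods describes the probability of prescribing given a test result and does not claim that each prescription responds to the test. An all-agent count also avoids reliance on indication codes, and drug code lists commonly sit in a fuller document. For antibiotics this stands. For antivirals it stands only in part: the article does not leave the drug list open but expressly includes all types, and the stated rationale concerns antivirals for patients with influenza.

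The magnitudes are also open to attack. The documents give no antiviral prescribing rate, name no antiviral for another virus, and do not show that such drugs would be prescribed or recorded in these primary care records. The large falls come from a very low assumed rate in negatives; on the absolute scale the change is small, and the odds ratio stays above 1 in every case shown. All of this stands, and it limits the claim to direction.

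A reader might infer that the 12.4% SARS-CoV-2 figure is the share of influenza-negative patients at risk of this error. It is not: it is a share of positive swabs in one week before the study.

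A reader might also infer that antibiotic results are seriously distorted by prophylaxis and unrelated infections. The documents do not support that. The sample-size outcome is tied to RTI consultations, the Abstract stratifies by relevant diagnosis and names bronchiectasis, the adjusted model includes chronic pulmonary disease, and a 7-day window is recorded beside the 30-day one. These soften the dilution without removing it.

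**Conclusion.** The point holds for antivirals. As written, the outcome counts antivirals that an influenza result is not meant to prompt, and those given for another respiratory virus fall mainly in the comparator. The direction, towards 1, follows from the definition provided that influenza antivirals are given more often to positives than to negatives. The size is unknown. The illustrative odds ratios show only that it could matter when prescribing in negatives is low, and they must not be read as an estimate of bias in this study. Nor can the whole of any fall be called differential, since part of it is plain dilution.

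For antibiotics the issue is minor and non-differential: 0.73 moves to 0.76–0.80 under assumed unrelated use of 3–10% in both groups, and the upper end has no support in the documents. The more useful observation is that Statistical Methods and Sample Size Calculation define the antibiotic outcome differently and should be aligned.

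**What to change.** **Antivirals.** Report them separately from antibiotics. Define the main antiviral outcome as influenza antivirals, using a drug list fixed before outcomes are analysed. Keep the any-antiviral count as a sensitivity analysis. Use of influenza antivirals should then not remain a covariate in that model unless it is defined as use before the swab.

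**Antibiotics.** Align Statistical Methods with the outcome in Sample Size Calculation, antibiotics prescribed at RTI consultations. Keep the all-antibiotic count. Add a sensitivity analysis that excludes repeat or prophylactic items already issued before the swab date.

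**What not to do.** Do not exclude antibiotics by an indication coded after the result is known. The result reaches the clinician in under 20 minutes, so it can influence a code entered the same day, and such an exclusion could itself differ between positives and negatives. Items issued before the swab are safe to exclude because the result cannot have affected them.

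**Cost.** One code list applied to prescribing data already being extracted, and slightly fewer counted events, hence somewhat less precision for the antiviral result.

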Antimicrobial prescribing and other study outcomes for those who have been swabbed will be obtained by linking information from the cobas Liat analyzer with data from the patient’s computerized medical record in primary care. We will demonstrate the feasibility of reporting antimicrobial stewardship and severe outcomes postinfection. Severe outcomes postinfection such as hospitalization and mortality will be obtained by linking the patient’s primary care computerized medical record to secondary care records at the national level including hospitalization and mortality data. A recent study used a linked cohort to study severe outcomes from COVID-19 infection [25].

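### The covariates of the adjusted prescribing model are chosen for influenza severity and omit prior antibiotic prescribing, so the positive-versus-negative odds ratio stays open to confounding by it

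*Protocol article*

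**What the plan says.** All of this is in the Methods of the protocol article.

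- **Outcome.** Statistical Methods plans the "crude odds of antimicrobial prescribing (all antibiotics and all antivirals regardless of type"), recorded within 7 or 30 days of the test.
- **Contrast.** The crude odds ratio comes from "dividing the odds of antimicrobial prescribing in people who receive a positive influenza POCT result by the odds in people who receive a negative test" (that is, a negative result).
- **Adjustment.** "We will also calculate the adjusted odds ratio using a logistic regression model", and then: "We will use the following set of covariates that are known to be associated with the severity of influenza and are collected from the routine" (health record data).
- **The list.** Age, sex, ethnicity, deprivation, chronic conditions, previous influenza vaccination, and two utilization counts: "number of GP visits in the 12 months prior to the study period describing a study participant’s health care–seeking behavior" and "number of hospitalizations in the 12 months prior to the study period (used as proxy for the severity of the chronic conditions"). It ends with "pregnancy, use of influenza antivirals, and pneumococcal and COVID-19 vaccination status".
- **Data source.** The section on face-to-face recruitment and testing states: "Antimicrobial prescribing and other study outcomes for those who have been swabbed will be obtained by linking information from the cobas Liat analyzer with data". The data meant are those of the primary care record.

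Two other places bear on the point. The Results paragraph of the Abstract plans to stratify the crude and adjusted odds by respiratory or other relevant diagnosis, with bronchiectasis as its example. The Limitations section names the nonrandomized design.

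**The concern.** A confounder of this odds ratio is a variable related both to being prescribed an antimicrobial and to testing positive. The selection rule asks instead for variables related to how severe influenza is. The two sets overlap, through age and chronic disease for example, but they are not the same. The visible consequence is that earlier antibiotic prescribing, a plausible predictor of being prescribed again, is absent.

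This is not a detail left to an unseen analysis plan, because the article states both the rule and the list.

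The adjusted odds ratio is a main part of the answer to the primary objective, and covariate adjustment is the main protection that the article offers for this contrast. If patients with a history of antibiotic courses are unevenly spread between test-positive and test-negative groups, part of a difference in prescribing would be credited to the test result when it belongs to the patients' history.

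**Working it through.** The article gives no figure on this point to reproduce. The check sets the list against what would be needed, then sizes the possible bias on stated assumptions.

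**1. Do the listed covariates stand in for prior antibiotic use?**

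- GP visits count contacts, and hospitalizations are offered as a proxy for chronic severity. Neither says whether an antibiotic was given.
- Both counts cover the 12 months before the study period, not before the swab. An antibiotic given between the study's start and the swab, including one for the same illness, falls outside both.
- Chronic conditions and the stratification by respiratory diagnosis record diagnoses, not courses of treatment.
- Use of influenza antivirals is not antibiotic history. It has no time window and overlaps the outcome.
- The eligibility section excludes only patients with an opt-out code or without consent, so recently treated patients enter the analysis unmarked.

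The listed items therefore control part of prior antibiotic use, not all of it.

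**2. How large could the bias be?**

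Assumed inputs, none from the article: 23% prescribed overall, 25% test-positive, 30% to 40% with prior antibiotic use, and prior use raising the odds of prescribing by a factor of 2 to 4. The test result has no effect. Let q0 and q1 be the share of prior users among negatives and positives, and r0 and r1 the prescribing risk without and with prior use. Then

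p0 = (1 − q0)·r0 + q0·r1, p1 = (1 − q1)·r0 + q1·r1, spurious OR = [p1/(1 − p1)] / [p0/(1 − p0)].

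q0, q1, r0 and r1 are solved so that the overall percentages and the two odds ratios hold.

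*Mild corner* (30% prior use, OR 2 with prescribing, OR 0.8 with a positive test): q0 = 0.3114, q1 = 0.2657, r0 = 0.1911, r1 = 0.3208.
- p0 = 0.6886 × 0.1911 + 0.3114 × 0.3208 = 0.2315
- p1 = 0.7343 × 0.1911 + 0.2657 × 0.3208 = 0.2255
- OR = 0.97

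*Extreme corner* (40% prior use, OR 4, OR 0.5): q0 = 0.4395, q1 = 0.2816, r0 = 0.1317, r1 = 0.3775.
- p0 = 0.5605 × 0.1317 + 0.4395 × 0.3775 = 0.2397
- p1 = 0.7184 × 0.1317 + 0.2816 × 0.3775 = 0.2009
- OR = (0.2009/0.7991) / (0.2397/0.7603) = 0.80

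| Prior use and positive test, OR | Spurious crude OR under no effect |
|---|---|
| 0.8 to 0.5 | 0.97 to 0.80 |
| 1.0 | 1.00 |
| 1.2 | 1.03 to 1.06 |

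A second set of assumptions used 26% positive (Table 1 has influenza as 215/818 = 26.3% of positive swabs, which is not the positivity among all swabs), 30% prior use and 40% prescribed among negatives. With OR 1.5 to 3 for prescribing and 0.8 to 0.5 for a positive test, it gives 0.98 to 0.87. The direction and order of size agree.

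**3. Would the covariate also sharpen the estimate?**

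With N = 1000, the second set of assumptions, a true OR of 0.6 and prior use unrelated to the test, the standard error of the log OR is 0.156 without the covariate and 0.157 to 0.161 with it. |z| moves from 3.24 to 3.25 (prior-use OR 1.5) or from 3.08 to 3.18 (prior-use OR 3). There is no gain in precision, and at most about 0.1 in |z|.

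**The case against.** The strongest reply is that this is one more plausible confounder in a study that already names its nonrandomized design as a limitation. Several parts of that reply stand.

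- The article contains no figure linking prior antibiotic use to the test result. With no link the bias is zero, and with a positive link it reverses. An antibiotic already given for the same illness could make a new prescription either more or less likely.
- The illustrated ratios are crude. Age, chronic pulmonary disease, immunosuppression, GP visits, hospitalizations and the planned stratification would remove some of the bias. How much cannot be computed from the article.
- If antibiotics and antivirals are pooled in one outcome, a positive result may itself raise antiviral prescribing. A bias in antibiotic prescribing then does not carry over one for one.

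A reader might also infer that the omission costs precision or power. The article does not support that. The familiar 1 − ρ² variance reduction belongs to linear models, while this is a logistic odds ratio, whose standard error rises slightly on adjustment. Nor should the bias be measured against the 80% power or the 5-point difference in Sample Size Calculation. Those concern the proportion of consultations with antibiotics, set beside an earlier difference between testing practices and the rest of the network, and are not tied to this contrast.

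Finally, it is tempting to call prior prescribing the baseline value of the outcome. It is patient history. The outcome belongs to a new infection episode.

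None of this answers the mismatch between the selection rule and the modelled outcome.

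**Conclusion.** The point holds as a possible confounding problem, not a demonstrated bias. The rule selects for influenza severity, the outcome is prescribing, and a plausible determinant of prescribing that the linked record can supply is left out. The listed proxies cover it only in part, and the utilization counts stop before the study period.

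The range from 0.80 to 1.06 rests wholly on assumed inputs and precedes any control by the other covariates. The lower end needs every assumption at its extreme. Neither the direction nor the size of the bias in the adjusted odds ratio can be stated from the article. The change is worth making because it is cheap and the estimate bears on the primary objective.

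**What to change.** In Statistical Methods:

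1. Add each patient's antibiotic courses in the 12 months ending the day before the swab, for example as 0, 1, or 2 or more.
2. Add a separate indicator for any antibiotic in the 30 days before the swab, so that treatment already given for the same illness can act in its own direction.
3. Reword the selection rule to covariates related to antimicrobial prescribing and to the test result.
4. Keep the model with the current list as a sensitivity analysis, so that the influence of the added variables can be seen.

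The cost is two or three more model parameters and one or two more variables from the record that already supplies the outcome. No additional patients, visits or procedures are needed.

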### Case Definition of Eligible Patients

All patients registered within the PIAMS study practice who do not have an opt-out code on their medical record and are showing symptoms of influenza-like illness (ILI), acute respiratory illness (ARI), or fever of higher than 37.5 °C will be eligible for the study if they consent to participate. We will use the European Centre for Disease Prevention and Control case definitions of ILI and ARI for this study. We will use the following exclusion criteria: (1) patient has an opt-out code on their medical record or (2) no informed consent.

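### The adjusted prescribing model selects covariates by influenza severity and includes nothing on the presenting illness, so the positive-versus-negative odds ratio can carry case-mix differences the test did not cause

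*Protocol article*

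**What the plan says.** The stated aim is causal in tone: "This study aims to report the impact of POCT for influenza on antimicrobial prescribing in primary care" (Objectives). Under Statistical Methods, the crude odds ratio for the primary objective divides the odds of prescribing in "people who receive a positive influenza POCT result by the odds in people who receive a negative test result". The outcome there pools antibiotics and antivirals of every type.

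The same section then specifies a logistic model with "the following set of covariates that are known to be associated with the severity of influenza". The list runs through age, sex, ethnicity, deprivation, chronic conditions, GP visits and hospital admissions in the previous year, and past influenza vaccination. It ends with "pregnancy, use of influenza antivirals, and pneumococcal and COVID-19 vaccination status". It has no item for syndrome, fever, symptom duration or site of infection.

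The population is mixed by design. Case Definition of Eligible Patients admits anyone "showing symptoms of influenza-like illness (ILI), acute respiratory illness (ARI), or fever" above 37.5 °C, and adds: "We will use the European Centre for Disease Prevention and Control case definitions of ILI and ARI for this study".

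Two other statements bear on the point. Statistical Methods promises "analysis of the demographic and clinical characteristics of those presenting with RTI symptoms", which is descriptive only. The Results paragraph of the Abstract promises odds ratios "stratifying by whether individuals have a respiratory or other relevant diagnosis (eg, bronchiectasis"; the Methods do not repeat this.

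**The concern.** A confounder of this odds ratio is something that comes before the test result and is related to both the result and the decision to prescribe. Association with influenza severity is a different criterion. It can admit variables that are unrelated to the test result, and it can leave out variables that matter.

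The presenting syndrome is the obvious candidate left out. It exists before the swab is taken, it plausibly changes the chance that the swab is positive, and a clinician weighs it when considering an antibiotic. If positives and negatives differ in syndrome mix, their prescribing will differ even if no clinician acts on the result. Because the odds ratio is offered as the answer to a question about the impact of testing, such a difference could be read as an effect of the test.

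**Working it through.** **No figure to reproduce.** The article gives no prescribing rate by syndrome, no positivity by syndrome and no syndrome mix. Every input below is therefore an assumption, and the calculation shows only what is possible.

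**Set-up.** Two syndrome groups, ILI and ARI, each half of those tested (w = 0.5). Positivity is p_I and p_A; antibiotic prescribing is a_I and a_A. Within each group prescribing does not depend on the result, so the true odds ratio is 1.00 in both.

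- Prescribing in positives: P+ = [w·p_I·a_I + (1−w)·p_A·a_A] / [w·p_I + (1−w)·p_A]
- Prescribing in negatives: P− = [w(1−p_I)·a_I + (1−w)(1−p_A)·a_A] / [w(1−p_I) + (1−w)(1−p_A)]
- OR = [P+/(1−P+)] / [P−/(1−P−)]

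**Case (a):** positivity 40% and 12%, antibiotics 20% and 45%.
- P+ = (0.200×0.20 + 0.060×0.45)/0.260 = 0.067/0.260 = 25.8%
- P− = (0.300×0.20 + 0.440×0.45)/0.740 = 0.258/0.740 = 34.9%
- OR = 0.347/0.535 = 0.65

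**Case (b):** positivity 35% and 10%, antibiotics 20% and 35%.
- P+ = (0.175×0.20 + 0.050×0.35)/0.225 = 0.0525/0.225 = 23.3%
- P− = (0.325×0.20 + 0.450×0.35)/0.775 = 0.2225/0.775 = 28.7%
- OR = 0.304/0.403 = 0.76

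**Case (c):** positivity 30% and 15%, antibiotics 20% and 30%.
- P+ = (0.150×0.20 + 0.075×0.30)/0.225 = 0.0525/0.225 = 23.3%
- P− = (0.350×0.20 + 0.425×0.30)/0.775 = 0.1975/0.775 = 25.5%
- OR = 0.304/0.342 = 0.89

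**A second parametrisation.** Assume the ILI share directly: 80% in positives and 50% in negatives, with antibiotics in 20% of ILI and 40% of other presentations.
- P+ = 0.8×0.20 + 0.2×0.40 = 24%
- P− = 0.5×0.20 + 0.5×0.40 = 30%
- OR = 0.316/0.429 = 0.74

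With ILI shares of 60–80% in positives against 50% in negatives, and assumed rates of 15–30% in ILI against 40–60% in others, the OR runs from 0.96 to 0.53. With the same mix in both groups it is 1.00. With syndrome in the model it is 1.00 by construction.

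**Effect of counting antivirals.** The outcome in Statistical Methods includes them. In case (c), suppose a further 10 percentage points of ILI patients, none of them given an antibiotic, receive an antiviral on clinical grounds whatever the result. Prescribing of any antimicrobial is then 20% + 10% = 30% in ILI and 30% in ARI, and the OR returns to 1.00. More than 10 points puts ILI above ARI and the OR above 1.

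**Does other text cover the gap?** Describing clinical characteristics does not adjust for them. The stratification in the Abstract has an underlying disease as its example; read broadly it might touch the presenting diagnosis, but it does not separate ILI from ARI. The Limitations section names the nonrandomized design without mentioning case mix between positives and negatives.

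**The case against.** **Direction.** A reader might infer that the odds ratio must fall below 1 and be mistaken for a stewardship benefit. The documents do not support that. The direction depends on unreported rates, reverses if ILI attracts more antibiotics, and can reverse for the pooled outcome once antivirals count.

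**Adjusted estimate.** The odds ratios above are unadjusted. Age, chronic pulmonary disease and other comorbidity, and GP visits are in the model and may absorb part of the bias. This stands: the calculation does not say what remains after adjustment.

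**Benchmark.** It is tempting to set the gaps against the 5- or 7-point differences under Sample Size Calculation. Those are motivated by practices using POCT compared with the rest of the network, which is a different contrast, so the comparison is not made here.

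**Availability of the data.** A reader might assume that syndrome is already classified at entry. The article does not say so. Eligibility lists the criteria without saying which one is recorded, the face-to-face recruitment section rules out any formal eligibility check, and Ethical Considerations lists only participant, site and result as held on the analyzer. Nor does the article say that ILI, ARI and fever are mutually exclusive, so the two separate groups in the calculation are a simplification.

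**Left to an analysis plan?** This does not stand. The article states both the selection rule and the list, so the point concerns what it fixes and not missing detail.

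**Conclusion.** The concern holds as a possible bias of unknown size and direction. The covariate rule is aimed at influenza severity when the model needs predictors of both test result and prescribing, and nothing in the list describes the presenting illness of a deliberately mixed population. For antibiotics alone, with no true effect and the three sets of assumed inputs, case mix by itself gives an unadjusted odds ratio of about 0.65 to 0.89. The wider assumed range in the second parametrisation gives 0.53 to 0.96.

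These figures rest on ILI being commoner among positives and attracting fewer antibiotics than other presentations, neither of which the documents establish. The change should be made because it is cheap and the odds ratio serves the primary objective.

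**What to change.** 1. Replace the selection rule: covariates should precede the test result and be expected to predict both the result and prescribing. Under this rule antiviral use belongs in the model only if it predates the test, since antivirals are also part of the outcome.
2. Add the presenting syndrome (ILI, ARI or fever criterion) as recorded before the result is known. If the routine record does not hold it, add a short field completed when the swab is taken or, for home swabs, at remote consent. Results are available in under 20 minutes, so a diagnosis code entered later in the consultation may already reflect the result. For patients already swabbed, use only what was recorded before the result and report how much is missing.
3. Report antibiotic odds ratios within ILI and within ARI where the categories can be separated, and keep antivirals apart in that display.

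The cost is a few degrees of freedom in a sample of up to 1000, a sentence or two of analysis text, and possibly one data item per swab. The change reduces confounding of the positive-versus-negative contrast. It does not turn that contrast into the effect of having POCT rather than no POCT, which needs an untested comparator.
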